### Experimental group: ERYT

The well-established cancer series “O-E-M-L-I-B-D” that is specific and standardized for breast cancer patients and which has been applied in breast cancer patients for decades will also be applied here [26, 32]. Through this indication-specific concept, the eurythmy therapy distinguishes itself from other mindful methods (e.g., tai chi). In Switzerland, eurythmy therapy is usually prescribed by physicians. Patients are treated by certified eurythmy therapists who have successfully completed a standardized 6 years of training, have passed a federal examination, and hold a federal diploma. For patients, eurythmy therapy is easy to learn and can be practiced anywhere (e.g., at home, at work, while traveling) and irrespectively of an individual medical condition or state of well-being. Eurythmy therapy also empowers patients by providing a tool that supports them in being active and self-reliant. The practices will be introduced using a standard progression from simpler to more challenging movements over the course of the intervention depending on the patients’ capabilities. Patients can perform and maintain the postures without stress and tension.

### Active control intervention: CoordiFit

The CoordiFit program consists of slow, standardized exercises that address physical coordination, stability, balance, and dexterity. These exercises serve as a control intervention and are non-specific with respect to CRF and breast cancer. They mimic the exercises of ERYT but have no mindfulness features. The exercises in the control group focus on movements such as mobilization of the backbone (roll down with the head toward the feet, vertebra by vertebra, coming back up, lastly with the head), the shoulders (roll shoulders, swing arms), legs (tap with one foot in front, sideward, and backwards, walking with tapping: coordinate the rhythm with the tap in a walking movement), balancing (standing and rocking on toes, positioning the arms, torso, and one leg parallel to the floor), and coordination exercises (clapping and tapping with hands and feet, respectively in different orders).

### Procedures

#### Screening (14–1 day(s) prior to allocation)

After providing the signed preliminary informed consent for completion of the FACIT-F questionnaire, the patient will be asked to fill in a printed version of the FACIT-F questionnaire in order to determine whether she is eligible for the study. The study nurse will enter the patient’s answers into the dedicated study database (REDCap). If the FACIT score is < 34, the patient will be offered a place on the study.

#### Allocation and baseline (14–0 day(s) prior to first training session)

After obtaining the patient’s signed informed consent, the patient will be randomized and the study nurse will fill in the Medical History and Treatments questionnaire in REDCap. The study nurse will contact the patient to specify which group she has been allocated to and will answer any questions the patient may have. Then, the study nurse will contact the therapist according to the group and area of the patient and ask her to call the patient to arrange the first training session. The patient will receive via email a link (generated by REDCap) to open in a web browser the questionnaires to be filled in (i.e., Patient’s Baseline questionnaire, PSQI, PHQ-9, GAD-7, BPI, NCCN Distress Thermometer, arm mobility, and PRFS). These questionnaires constitute the baseline assessment and consequently must be filled in before the first session.

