## Methods/design

### Study design

The ERYT/CoordiFit study is a randomized controlled, open-label, two-arm, multi-center superiority trial. A sample of 196 female patients with metastatic breast cancer presenting with CRF will be randomly allocated to the intervention or control group in a 1:1 ratio. The control group is an active control intervention (CoordiFit) in order to control for unintended effects such as the therapist-patient interaction and active engagement (being part of a program). It consists of slow, standardized exercises that address physical coordination, stability, balance, and dexterity. These exercises are non-specific with respect to CRF and do not include mindfulness features. The study is planned to be conducted in 14 centers across Switzerland.

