### Participants and recruitment

The participants will be recruited by oncologists from the departments of clinical oncology at each local study site. Our study will be advertised on the homepage of the Institute for Complementary and Integrative Medicine and flyers will be available at each study site. Subjects are only included if they meet a pre-defined FACIT-F subscale score. To avoid bothering subjects by fully informing them about a study for which they prove ultimately ineligible, a two-step consenting procedure is implemented:
Each potential participant will first be asked to sign a short “preliminary consent” form for completion of the FACIT-F questionnaire. The oncologist or a study nurse will explain to the patient briefly the nature of the study and its purpose and inform her that she might be eligible for the study depending on her FACIT-F subscale score. The preliminary consent form signed by the patient and by the oncologist or the study nurse will be documented in the patient’s source documentation.Eligible patients will then be offered to participate in the study and, if interested, will be fully informed about the trial using the full patient information and informed consent form. Written informed consent will be obtained before the participant is submitted to any study procedure. The patient has at least 24 h to consider whether to participate and can subsequently send back the signed consent form by post to the study site (a stamped, addressed envelope will be provided). A study nurse will contact the patient by phone after 6 working days if a patient does not send back the consent form. Information on the schedule of study procedures and assessments are shown in Table 1.

**Table 1 Tab1:** Schedule of enrollment, interventions, and assessments

Study period	Screening	Baseline	Intervention													Follow-up	
Time	14–1 days prior to baseline	0 (14–0 days prior to first training session)	Week 1	Week 2	Week 3	Week 4	Week 5	Week 6	Week 8	Week 10	Week 12	Week 14	Week 16	Week 18	Week 20	+ 6 months after week 20	+ 12 months after week 20

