#### Statistical analysis

A nonparametric ANOVA model for longitudinal data, the F1-LD-F1 model of Brunner, Domhof, and Langer, will be applied to model the course of the FACIT-F subscale scores from baseline over the whole intervention [77]. The first F1 means that there is one group factor, the second that there is one-time or repeated measures factor. The main hypotheses are the following:

H0: there is no interaction of the treatment arm with the time;

H1: there is an interaction of the treatment arm with the time (favoring ERYT).

Least-square means of the original data (original scales) and 95% confidence intervals will be calculated and displayed in figures over time.

Differences from baseline to end of intervention will be analyzed by stratified Wilcoxon rank-sum tests (via ordinal logistic regression, i.e., proportional odds model with baseline measurements as co-variable, treatment arm as binary predictor and differences as outcome variable). Least-squares means of the original differences and 95% confidence intervals will be calculated.

Exploratory endpoints will be analyzed descriptively using mean and standard deviation or median and interquartile, as appropriate.

Statistical analysis will be conducted applying an intention-to-treat approach, and therefore including all randomized patients. In case of protocol non-adherence, a per-protocol analysis will be conducted to estimate the robustness of the primary estimates. All tests will be two-sided with a significance level of 0.05. Statistical analysis will be performed using R [78].

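### Baseline forms for six secondary scores are sent after the patient has been told her arm, so those baselines can differ by arm; the primary FACIT-F endpoint is not affected

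*Protocol article*

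**What the plan says.** The protocol article describes a "randomized controlled, open-label, two-arm, multi-center superiority trial" (Study design). Its section Allocation and baseline sets out these steps:

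- Randomisation follows consent directly: "After obtaining the patient’s signed informed consent, the patient will be randomized".
- The arm is disclosed: "The study nurse will contact the patient to specify which group she has been allocated to".
- A therapist of the allocated discipline is brought in to phone the patient: "Then, the study nurse will contact the therapist according to the group and area of the patient".
- An e-mailed REDCap link opens the forms: "Patient’s Baseline questionnaire, PSQI, PHQ-9, GAD-7, BPI, NCCN Distress Thermometer, arm mobility, and PRFS".
- Their status and deadline are given as: "These questionnaires constitute the baseline assessment and consequently must be filled in before the first session".

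Table 1 agrees. Randomisation and these forms share the Baseline column, and the FACIT-F alone among the outcome questionnaires sits under Screening. Under Endpoints, the secondary list defines change from baseline in FACT-G, PSQI, BPI, PHQ-9, GAD-7, the Distress Thermometer and arm mobility, with the baseline measurement included. Under Statistical analysis, differences from baseline to end of intervention go into a "proportional odds model with baseline measurements as co-variable", so baseline enters both as covariate and inside the outcome.

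**The concern.** A baseline is protected by randomisation only if it is fixed before allocation can influence it. Here a patient who already knows whether she will receive eurythmy or the control programme rates her own mood, anxiety, distress, pain, sleep and arm mobility. Relief or disappointment could move those ratings, and the movement would pass into the change score as an apparent treatment difference. The sign is open: a control group that reports worse after disappointment would later seem to improve more, while other reactions would favour eurythmy. The shift could create an effect or hide one.

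Missing data are a second route. Nothing requires complete baseline forms before allocation, so a patient unhappy with her arm may not return them, and the set of patients with a usable baseline could then differ by arm.

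**Working it through.** **Order of events.** The article gives: FACIT-F on paper at screening; full consent; randomisation; disclosure by the nurse; contact with the therapist; link to the remaining forms. The sequence word in the text attaches to the therapist contact, not to the link, so a particular patient might answer before she is told. Disclosure first is the natural reading, and nothing in the text or Table 1 prevents it.

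**Endpoints exposed.** Score-based secondary endpoints are week-20 FACIT-F, FACT-G, PSQI, BPI, PHQ-9, GAD-7, Distress Thermometer and arm mobility: 8. The FACIT-F questionnaire contains the FACT-G (Outcome measures) and is completed at screening, which removes the first two: 8 − 2 = 6 exposed. Adding return to work, retention, compliance and metabolomics gives 8 + 4 = 12 secondary items, so 6 of 12 overall. PRFS is also collected after disclosure but is not a listed endpoint.

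**Sample size used.** The plan's figure reproduces: 156 / (1 − 0.20) = 195, or 196 for equal arms. Evaluable patients per arm: 156 / 2 = 78.

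**Illustration.** Assumptions, none of them in the documents: no true effect; disclosure shifts one arm's baseline by s (in SD units) and leaves follow-up unmoved; equal SDs; correlation r between baseline and follow-up of 0.5 to 0.7; normal approximation; two-sided 5% test.

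- Unadjusted change: bias s, SE = √(2(1 − r) × 2/78). This is 0.160 at r = 0.5 and 0.124 at r = 0.7.
- Baseline-adjusted: bias r × s in absolute size, SE = √((1 − r²) × 2/78). This is 0.139 at r = 0.5 and 0.114 at r = 0.7.
- Error rate = P(|Z + bias/SE| > 1.96).

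| Shift s | r | Unadjusted: bias/SE | Error rate | Adjusted: bias/SE | Error rate |
|---|---|---|---|---|---|
| 0.1 | 0.5 | 0.1/0.160 = 0.62 | 9.6% | 0.05/0.139 = 0.36 | 6.5% |
| 0.1 | 0.7 | 0.1/0.124 = 0.81 | 12.7% | 0.07/0.114 = 0.61 | 9.4% |
| 0.2 | 0.5 | 0.2/0.160 = 1.25 | 23.9% | 0.10/0.139 = 0.72 | 11.1% |
| 0.2 | 0.7 | 0.2/0.124 = 1.61 | 36.4% | 0.14/0.114 = 1.22 | 23.2% |

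Adjustment reduces the distortion but does not remove it, because the covariate itself carries the shift. The adjusted columns are the closer analogue of the stated method for differences, which includes baseline as a covariate. Neither formula represents the F1-LD-F1 model, which the article specifies for the FACIT-F subscale.

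**The case against.** Several counter-arguments have force.

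- **The primary result.** A reader might infer that the trial's main conclusion is compromised. It is not: the FACIT-F is answered at screening, before randomisation. The Discussion does name sleep, pain, anxiety, depression and distress as confounders or effect modifiers, and says that potential confounders will be taken into account. However, the stated primary model has only the group and time factors, so the article does not show that post-disclosure scores enter it.
- **Whether a shift occurs.** A reader might also infer that these comparisons are biased. The documents show only that they can be. The comparator is an active programme with the same schedule and similar movements, so strong disappointment is less likely than with a waiting list. The PSQI looks back over 4 weeks, which dampens the effect of a recent phone call.
- **The figures.** They assume that only baseline moves. If a fraction k of the reaction persists to follow-up, the unadjusted bias falls to (1 − k)s, and the adjusted bias becomes (r − k)s in place of r × s. The percentages are therefore illustrations, not predictions.
- **Missing baselines.** Automatic reminders and therapist prompts limit non-return. Differential loss is possible but not demonstrated.
- **A fallback exists.** Post-baseline scores can be compared between the randomised arms without the exposed baseline.

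These points limit the reach and size of the problem. They do not change the described order, and no other section places the forms earlier.

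**Conclusion.** The point stands as a weakness in the secondary endpoints. As written, six self-reported secondary scores take their baseline after the patient knows her arm, with no safeguard beyond completion before the first session. Under the stated assumptions, the nominal 5% error rate would be about 7 to 23% with baseline adjustment and 10 to 36% for unadjusted change; the true shift, its sign and the correlations are unknown. To say that most secondary endpoints are exposed is fair only for the score-based ones (6 of 8), since it is half when every secondary item is counted (6 of 12). Grade: should-fix. It is worth acting on because a baseline taken after disclosure cannot be recovered later.

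**What to change.** Send the REDCap baseline link at full consent, and require the forms to be completed either

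1. before the randomisation function is released, or
2. as a lighter option, before the nurse discloses the arm and the therapist calls.

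Reorder the section Allocation and baseline to match, and in Table 1 place the questionnaires ahead of randomisation (option 1) or state that they precede disclosure (option 2). Baseline reminders should come from the automatic e-mails or the nurse, because a prompt from the therapist would reveal the arm. Under option 2, state what happens when the reminders run out: for example, record the baseline as missing and then disclose, so that missingness cannot depend on knowing the arm.

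**Cost.** No extra visit or questionnaire is needed, and REDCap already runs both the links and the allocation. Option 1 uses the screening window of 14 to 1 days before allocation, not the 14 to 0 day window, which runs from baseline to the first session. Postal consent may be chased only after 6 working days (about 8 calendar days), and the questionnaire reminders run to 2 + 5 = 7 days. A slow responder could thus need 8 + 7 = 15 days, so the window may need a small allowance. Option 1 would also lose a few consenting patients who never complete the forms. Option 2 keeps them and need not lengthen screening.

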#### Session 1 (week 1)–session 13 (week 20): intervention, assessment tools/questionnaires, and patient diary

During the intervention phase, the patient will perform 13 sessions of ERYT or CoordiFit. During the whole intervention phase, regular physical activity (at least once a week) and compliance with home training will be reported by the patient in a pre-printed diary which will be provided to the patient. The patient will send back the diary by postal mail after the last session (addressed and stamped envelope will be provided by the study site). At each session, the eurythmy or physical therapist will record in REDCap whether the patient attended, the reason if not, and if the patient was able to execute all movements (therapist’s questionnaire).

#### Sessions 7 and 10 (weeks 8 and 14): assessment tools/questionnaires

At weeks 8 and 14, the patient will receive via email a link (generated by REDCap) to open in a web browser the questionnaires to be filled in (FACIT-F, PSQI, PHQ-9, GAD-7, BPI, NCCN Distress Thermometer, and arm mobility).

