### Endpoints

The primary endpoint of the study is the change from baseline over the whole intervention period (i.e., including measurements at baseline, weeks 8, 14, and 20) in the Functional Assessment of Chronic Illness Therapy – Fatigue (FACIT-F) subscale.

Secondary endpoints are the following:
The change from baseline to the end of intervention (i.e., including measurements at baseline and at week 20) in the FACIT-F subscaleThe change from baseline over the whole intervention period (i.e., including measurements at baseline, weeks 8, 14, and 20) in the FACT-G, Pittsburgh Sleep Quality Index (PSQI), Brief Pain Inventory (BPI), Patient Health Questionnaire-9 (PHQ-9), General Anxiety Disorder-7 (GAD-7), NCCN Distress Thermometer, and arm mobility scores.Number of patients who return to work during the intervention phase or the follow-up.Retention will be measured by the number, period to, and reasons for attrition for each group. Compliance will be measured by the number of sessions attended, and the number of hours of home training per week.Targeted quantitative metabolomics will be investigated in 30 patients as a translational research element. Analysis of amino acids, organic acid profiles, and acylcarnitine profiles in serum and urine will be measured with high-performance liquid chromatography and liquid chromatography-mass spectrometry, allowing for analysis of over 100 metabolites. Metabolomic data will be measured at baseline and at the end of intervention (week 20).

Exploratory endpoints of the study are follow-up measurements (6- and 12-month follow-up from week 20) in FACIT-F subscale, FACT-G, NCCN Distress Thermometer, PSQI, BPI, PHQ-9, GAD-7, and arm mobility.

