#### Six- and 12-month follow-up assessments (from week 20)

Finally, the patient will receive via email a link (generated by REDCap) to open in a web browser the questionnaires to be filled in at 6-month and 12-month follow-up (Patient’s Follow-up questionnaire, FACIT-F, PHQ-9, GAD-7, BPI, NCCN Distress Thermometer, arm mobility, and PRFS). After the 12-month follow-up assessment, the study nurse will fill in the questionnaire “End of Study”. The same procedure will be followed in case of withdrawal.

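### Table 1 omits PHQ-9 and GAD-7 at weeks 8 and 14, and the follow-up text omits PSQI, both against the endpoint list

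*Protocol article*

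**What the plan says.** The Endpoints section sets what has to be measured. One group of secondary endpoints is the change over the whole intervention, using baseline and weeks 8, 14 and 20. That group includes "Patient Health Questionnaire-9 (PHQ-9), General Anxiety Disorder-7 (GAD-7), NCCN Distress Thermometer, and arm mobility scores", and PSQI is in it too. The exploratory endpoints are the 6- and 12-month measurements "in FACIT-F subscale, FACT-G, NCCN Distress Thermometer, PSQI, BPI, PHQ-9, GAD-7, and arm mobility".

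The Procedures section then says what is e-mailed to the patient at each time. At weeks 8 and 14 the link covers "the questionnaires to be filled in (FACIT-F, PSQI, PHQ-9, GAD-7, BPI, NCCN Distress Thermometer, and arm mobility"). At 6 and 12 months it covers "Patient’s Follow-up questionnaire, FACIT-F, PHQ-9, GAD-7, BPI, NCCN Distress Thermometer, arm mobility, and PRFS". PSQI is not in that follow-up list.

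Table 1 gives the same schedule as a grid. Its joint row for PHQ-9 and GAD-7 is marked at baseline, week 20, 6 months and 12 months, and is blank at weeks 8 and 14. Its PSQI row is marked at baseline, weeks 8, 14 and 20, and both follow-ups.

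**The concern.** Neither the table nor the text, used alone, delivers every measurement that the Endpoints section calls for. Table 1 is short on depression and anxiety during the intervention. The follow-up text is short on sleep quality afterwards.

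This matters because of how the data are collected. Questionnaires reach patients as REDCap links, and the Discussion says that the study schedules no hospital visits during the intervention and follow-up periods. A questionnaire left out of the survey schedule would have no study visit at which it could be picked up. PSQI asks about the preceding 4 weeks, so a missed one cannot be reconstructed later. The Discussion also names sleep, anxiety and depression among the major confounders or effect modifiers of fatigue, so these instruments are not incidental to the trial.

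**Working it through.** There is no figure of the plan's own to reproduce here. The check sets the three statements of the schedule side by side.

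**Is Table 1 readable?** Each assessment row checked (FACIT-F, PSQI, PHQ-9/GAD-7, BPI, Distress Thermometer, arm mobility) has 18 fields: one label plus 17 time columns, as in the header. The PSQI, BPI, Distress Thermometer and arm mobility rows all show weeks 8 and 14 in the right columns. The blanks in the PHQ-9/GAD-7 row are therefore not a sign of damage in text extraction. The PSQI omission is in running prose, where table damage cannot be the cause.

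**Comparison** (0 = baseline; numbers are weeks; +6 and +12 are months after week 20):

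| Instrument | Endpoints section | Table 1 | Procedures text |
|---|---|---|---|
| PHQ-9, GAD-7 | 0, 8, 14, 20, +6, +12 | 0, 20, +6, +12 | 0, 8, 14, 20, +6, +12 |
| PSQI | 0, 8, 14, 20, +6, +12 | 0, 8, 14, 20, +6, +12 | 0, 8, 14, 20 |
| BPI, Distress Thermometer, arm mobility | 0, 8, 14, 20, +6, +12 | all six | all six |

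FACIT-F, which carries the primary endpoint and FACT-G, is given the same times in Table 1 and in the text: screening, weeks 8, 14 and 20, and both follow-ups. This discrepancy does not touch it.

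**Gaps against the Endpoints section**

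- Table 1: PHQ-9 and GAD-7 lack weeks 8 and 14. That is 2 of the 4 intervention-period measurements, 2 of the 3 after baseline within the intervention, or 2 of 5 after baseline if the follow-ups are counted.
- Procedures text: PSQI lacks both follow-up measurements, 2 of 2.

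**Number of questionnaires at stake**

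- Table 1 followed, all randomised patients: 2 instruments × 2 visits × 196 = 784.
- Follow-up text followed, all randomised patients: 1 instrument × 2 visits × 196 = 392.
- With the 156 patients whom the sample size section expects after drop-out: 2 × 2 × 156 = 624 and 1 × 2 × 156 = 312.

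All four counts are upper limits, because they assume that every patient counted returns every form.

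**Which reading do the documents support?** In each case two places agree and one stands alone. For PHQ-9 and GAD-7 at weeks 8 and 14, Endpoints and the text agree against Table 1. For PSQI at follow-up, Endpoints and Table 1 agree against the text. The intended schedule can therefore be recovered from the article itself.

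**The case against.** The strongest reply is that this is an editorial slip whose answer is already on the page. The Endpoints section settles both cases, and the week 8 and 14 text combined with the follow-up columns of Table 1 supplies every listed endpoint. Sites choose no version either: REDCap sends the links automatically, and the system goes live only after a formal test. The article condenses protocol version 2-1, which is not shown, so nothing here proves that the live schedule has either gap. All of this stands. It limits the consequence but does not remove the contradiction, since the article does not say against which schedule the system was tested.

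Three stronger readings are tempting and are not supported.

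- A reader might infer that stated endpoints fail whichever version is used. That is true only if Table 1 alone, or the Procedures text alone, is adopted as a whole.
- A reader might infer that the planned longitudinal model could not be fitted for PHQ-9 and GAD-7. The Statistical analysis section names the F1-LD-F1 model only for the FACIT-F subscale. A model with one group factor and one time factor can in any case be fitted with two time points. The same section describes an analysis of change from baseline to the end of the intervention, which needs only baseline and week 20. What would be lost is the intermediate course.
- A reader might take the PSQI gap as damage to a main result. The 6- and 12-month measurements are exploratory and analysed descriptively. The PSQI secondary endpoint, over baseline and weeks 8, 14 and 20, is consistent in all three places.

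**Conclusion.** The point holds as an internal contradiction in the assessment schedule. Table 1 conflicts with the Endpoints section and the week 8 and 14 text on PHQ-9 and GAD-7. The 6- and 12-month text conflicts with the Endpoints section and Table 1 on PSQI.

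The consequence is conditional on which statement the live survey schedule follows, and the article does not show that. Under Table 1, two secondary endpoints lose their two intermediate measurements and cannot be computed over four time points as defined, but the change from baseline to week 20 survives. Under the follow-up text, one exploratory, descriptive endpoint has no data. The primary endpoint and its power are untouched. The point is worth correcting because uncollected questionnaires cannot be recovered and the correction is nearly free. It does not threaten the main result of the trial.

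**What to change.** Take the Endpoints section as the reference and bring the other two places into line with it:

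1. In Table 1, mark PHQ-9 and GAD-7 at weeks 8 and 14.
2. In the text on the 6- and 12-month assessments, add PSQI to the list of e-mailed questionnaires.
3. Compare the REDCap survey schedule with the corrected table. If patients have already been enrolled, record which questionnaires were actually sent at each time.

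The cost is two edits and one check. If the live schedule already sends everything, patients notice nothing. If it had omitted them, the added burden is at most 9 + 7 = 16 short items at each of two visits, and one 19-item PSQI (5 to 10 minutes by the article's own estimate) at each follow-up.
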